**Methods:**

This is an exploratory mixed methods study to identify predictors and moderators of health literacy in the Deaf population. These predictors of health literacy will be used to inform the second step that qualitatively explains the findings, including how Deaf individuals access and understand Web-based health information. Multiple interviewer- and computer-based instruments underwent translation and adaptation, from English to ASL, to make them accessible for the Deaf participants in our study. A planned sample of 450 Deaf ASL users and 450 hearing native English speakers, aged 18 to 70 years, will be recruited from 3 partnering sites: Rochester, NY; Flint, MI; and Chicago, IL. These individuals will participate in a single data collection visit. A subset of participants (approximately 30) with key characteristics of interest will be invited for a second data collection visit to observe and inquire more about their ability to directly access, navigate, and comprehend Web-based health information. The study will help assess how the ways health literacy and information are visualized may differ between Deaf individuals and hearing individuals. The study will also survey participants’ ownership and use of computer and mobile devices and their level of Web-based information use, including health information.

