## Methods

### Overview

For this study, there are 3 proposed aims. Aim 1 is to evaluate differences in ASK, regarding health information for both Deaf signers and hearing English speakers. Aim 2 plans to assess hearing status as an effect modifier of the association between health literacy and ASK with health information. Aim 3 will qualitatively assess the impact of health information accessibility and patterns of use on health literacy with one-on-one elicitation interviews. This will be based on actual Web-based health information searches for 4 clinical vignettes using an observed task fulfillment experiment as a prompt. The goal of this aim is to explore differences with Web-based health information search ability and health knowledge acquisition in a subsample of Deaf and hearing individuals recruited from aims 1 and 2. The University of Michigan institutional review board (IRB) approved the study and provides coordination with the following IRBs: Sinai Hospital, Rochester Insitute of Technology, and Hurley Medical Center (HMC). The study is also registered at the ClinicalTrials.gov under ID NCT03093779.

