### Study Design

The study uses an explanatory sequential mixed methods design [24] with extensive quantitative data collection procedures to identify predictors and moderators of health literacy. We will first conduct a cross-sectional study to collect predictors of health literacy. These predictors of health literacy will be used to inform the subsequent phase of qualitative assessment. For example, elicitation interviews with selected participants returning for the second data collection visit will be used to help explain the quantitative results and to help elucidate how Deaf individuals access and understand Web-based health information. The study will use a stratified sampling approach to invite participants of certain characteristics to return for further data collection. Characteristics of interest will be based on quantitative analyses that show significant associations between health literacy and any of the measured variables (eg, educational attainment, age, or reading literacy). Approximately 15 Deaf and 15 hearing participants with inadequate health literacy and another 15 Deaf and 15 hearing participants with adequate health literacy will return for a second visit to conduct a task performance on a desktop computer and participate in a follow-up interview designed to learn more about their decision making and preferences. The return visit will involve a qualitative assessment using elicitation interviews to help explain any of the quantitative results. The goal is to learn how and why Deaf individuals access and understand health information (Figure 2) and how this may differ from hearing individuals.

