The recordings from the task performance above will serve as a prompt for the elicitation interview. It will help inform the subsequent qualitative assessment to help explain the quantitative results (of aims 1 and 2) and elucidate how and why Deaf individuals access and understand health information. Similarly, the same approach will be conducted with a subsample of hearing individuals. This will be done to provide robust comparisons. Video-based and semistructured qualitative assessments will be used to determine both how and why Deaf and hearing participants of different health literacy strata (inadequate and adequate; n=15 each) may differ in their performances with Web-based health information searches. The findings here will be used to help explain results from aims 1 and 2. The elicitation interview questions will be generated initially from the findings in aims 1 and 2 and complemented with additional questions following completion of the task performance on a computer. The interviewer will playback the dual-screen recording of the participant’s actions to facilitate recall of his or her own actions and thoughts with each task undertaken. The interviewer will encourage the participant to make his/her thoughts transparent, that is, telling how and why the choices were made in a narrative format. The dual-screen recording with performance metrics will serve as stimulus material for the video elicitation interview. As the dialog between the interviewer and the participant will be in ASL (visual language), a separate external video camera will be used to record this interaction for later transcription. The interview will reveal the complex cognitive and decision-making processes that may occur with each individual, which are not adequately revealed in earlier statistical analysis. The incorporation of both steps provides better integration of the findings of all 3 aims and generates robust data to guide future intervention development to address inadequate health literacy and information marginalization for Deaf populations. A strength of this step is the ability to explore contextual factors (ie, task- and user-oriented factors) that could not be explained with the first visit. As stated by a newer eHealth literacy model [45], these task- and user-oriented factors are important in their roles in the overall eHealth context. The proposed step will help examine how these intrapersonal and system-based factors may shape the Web-based health experience and abilities for both Deaf and hearing individuals.

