
**Table 2 table2:** Aim 3 approaches.

Definition	Purpose	Approach	Data collection	Expected outcomes
Web-based health information navigation and comprehension (step 1)	To assess Web-based health information search ability, acquisition, and patterns	Use of Tobii video/online use recording software; 4 clinical vignettes with questions to prompt Web-based search	Navigation patterns of Deaf individuals; preferences of health websites, including search engines (n=15 Deaf and n=15 hearing for comparison); scoring on questions related to vignettes	Assess Web-based health information search ability of Deaf individuals (unknown); determine if Deaf individuals’ health literacy determines the quality of the navigation and comprehension of the information (unknown); generate areas of weaknesses and strengths for interventions to focus (unknown)
Elicitation interviews (step 2)	To explain and expand the understanding of the findings demonstrated in aims 1 and 2	Use of elicitation interviews about video recordings of the participants and their Web-based searches	Explore how and why participants decided to use the websites they chose, including the types of queries and what aspects of the Web-based information was useful to them	Assess how Deaf individuals visualize and learn Web-based health information (unknown); determine the preferences of health information tools and dissemination (unknown) and understand why they have those preferences (unknown)

### Statistical Analyses for Aim 1

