Building on the methodology used in previous Web-based search behavior studies [46], participants’ search skills and success in addressing the clinical scenario tasks will be assessed using a combination of methods. First, based on the browser log and interaction data gathered by the usability software, we will compute summary statistics, such as the total time (in minutes) spent in searching, the number of unique websites and pages visited, and the number and characteristics of queries issued, involved in completing each task. Second, we will include time-based retrieval measures [47] that can characterize and quantify how a participant’s search progress evolves over time. Knowledge acquisition will be measured by the number of correct responses based on the clinical vignettes (score range between 0 and 12). All measures representing navigation skill and knowledge acquisition will be compared across levels of health literacy (adequate vs intermediate/inadequate) on the subgroup of the preselected 30 Deaf participants using 2 sample *t* tests. Although it is anticipated that power will be low to observe statistical significance, the primary objective for this comparison is to identify trends. Search progress for the clinical scenarios will be defined in terms of the quality of health information pages found during the search task. To assess the quality of health information pages, the research team will evaluate the Web pages/resources returned by participant searches or visited by the participant via browser navigation in terms of accuracy and coverage of the target facts in the reference set. Any differences will be discussed until a consensus is obtained.

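### Aim 3 collects hearing comparators for the Web search tasks, but its only stated test uses the Deaf participants alone, with a literacy grouping that does not match the sampling

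*Protocol article*

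**What the plan says.** The Overview of the Methods states that the goal of Aim 3 is to "explore differences with Web-based health information search ability and health knowledge acquisition in a subsample of Deaf and hearing individuals". Study Design sets the return-visit sample by hearing status and literacy: "Approximately 15 Deaf and 15 hearing participants with inadequate health literacy and another 15 Deaf and 15 hearing participants with adequate health literacy". Procedures for Return Visit explains why hearing people are included: "Similarly, the same approach will be conducted with a subsample of hearing individuals. This will be done to provide robust comparisons". It also says that the qualitative assessments will determine "how and why Deaf and hearing participants of different health literacy strata (inadequate and adequate; n=15 each) may differ in their performances". Table 2 lists "n=15 Deaf and n=15 hearing for comparison" under data collection for the search task.

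Analyses for Aim 3 then describes summary statistics and time-based search measures for participants in general. For inference, all navigation and knowledge measures are to be "compared across levels of health literacy (adequate vs intermediate/inadequate) on the subgroup of the preselected 30 Deaf participants", by two-sample t tests. The same paragraph concedes that power will be low and says that the purpose is to identify trends. No test or contrast involving hearing participants is stated.

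Statistical Analyses for Aim 2 defines three literacy categories from the Newest Vital Sign score: adequate (5-6), indeterminate (2-4) and inadequate (0-1). The Aim 3 size is stated differently elsewhere. The Methods paragraph of the Abstract has "A subset of participants (approximately 30) with key characteristics of interest" returning in total.

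**The concern.** Two separate things do not fit together.

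First, goal and sampling are comparative across hearing status, but the stated test is not. A test restricted to Deaf participants cannot estimate a Deaf-hearing difference. As planned, search time, sites visited, query counts and the 0-12 knowledge score would be measured in hearing participants without entering any stated quantitative contrast. At stake is whether the study reports an estimate, with its uncertainty, for a question that it names as the goal of this aim.

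Second, the grouping in the test includes a middle literacy level that Study Design and Procedures for Return Visit do not list among the strata, and that Aim 2 calls by another name. Either the middle level is empty and the label is wrong, or people scoring 2-4 are to be invited and the sampling description is wrong. Those selecting participants and those analysing the data could read this differently. This second point has no bearing on whether Deaf and hearing participants can be compared.

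**Working it through.** **Reproducing the plan's figure.** Study Design gives 15 Deaf inadequate + 15 Deaf adequate = 30 Deaf, which agrees with the 30 Deaf participants in Analyses for Aim 3. Adding 15 + 15 hearing gives 60. Under this sampling nobody scoring 2-4 is invited, so the pooled lower group is simply the 15 inadequate participants and the planned test is 15 against 15.

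**Size of Aim 3 as stated in each place.**

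| Place | Stated size |
|---|---|
| Abstract, Methods | about 30 in total |
| Study Design | 4 cells of about 15 = 60 |
| Procedures for Return Visit | 15 for each stratum; not clear whether within each hearing group |
| Table 2 | 15 Deaf + 15 hearing = 30 |
| Analyses for Aim 3 | 30 Deaf |

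Study Design and Analyses for Aim 3 agree on 30 Deaf participants; the Abstract and Table 2 agree on 30 in total. These cannot both hold.

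**Assumptions.** The protocol gives no significance level, SD or effect size for Aim 3. I take a two-sided 5% level, a common SD and normally distributed measures, and express everything in SD units.

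**Precision.** The 95% half-width for a difference between two groups is t(0.975, df) × √(1/n₁ + 1/n₂).

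- Planned Deaf-only literacy test, 15 vs 15, df 28: 2.048 × √(2/15) = 2.048 × 0.365 = 0.75 SD. The difference detectable with 80% power is 1.06 SD; power is about 26% for a difference of 0.5 SD and 56% for 0.8 SD. This fits the protocol's own remark that power will be low.
- The same Deaf literacy contrast taken as a simple effect from a four-cell model, 15 per cell, df 56: 2.003 × 0.365 = 0.73 SD. Adding the hearing data barely sharpens it.
- Deaf-hearing contrast if Study Design holds, 30 vs 30, df 58: 2.002 × √(2/30) = 2.002 × 0.258 = 0.52 SD. Detectable difference 0.74 SD; power about 48% at 0.5 SD and 86% at 0.8 SD.
- Deaf-hearing contrast if Table 2 holds, 15 vs 15: about 0.75 SD, with a detectable difference of 1.06 SD.
- Hearing-by-literacy interaction, 15 per cell: the standard error is √(4/15) = 0.516 SD, so the detectable difference is (1.960 + 0.842) × 0.516 = 1.45 SD (normal approximation).

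**Planned against possible.** In the stated test the number of hearing participants is zero, so no Deaf-hearing estimate results under either reading of the sample size. With the contrast added, one is available at ±0.52 SD or ±0.75 SD.

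**The case against.** The strongest defence is that Aim 3 is mainly qualitative. The Overview says so, and Procedures for Return Visit assigns the Deaf-hearing question to video-based and semistructured assessment. The interview analysis looks for themes across participants and links them to the quantitative data in joint displays. The summary statistics are not restricted to Deaf participants either. This stands: a reader might infer that Aim 3 cannot show how Deaf and hearing searchers differ, and the protocol does not support that. What is missing is a quantitative contrast of the task measures.

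It can also be said that the Deaf-only test answers a question of its own. Table 2 lists whether literacy among Deaf individuals determines the quality of their navigation and comprehension. This stands too. A reader might infer that leaving out hearing participants throws away half the information on that effect. It does not: hearing data inform a Deaf literacy effect only if the effect is assumed equal in both groups, and without that assumption the half-width moves only from 0.75 to 0.73 SD.

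A reader might further infer that middle scorers will dilute the low-literacy group. That would happen only if people scoring 2-4 were invited, which the sampling text does not provide for, though it does not expressly exclude them.

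Finally, the test is labelled trend-seeking and the article condenses a fuller protocol. The caveat explains the low power but not the absence of the comparator; a trend-seeking Deaf-hearing estimate would serve the same purpose. Nor is this merely omitted detail, since the article fixes the population, grouping, measures and test.

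**Conclusion.** The point holds for the planned quantitative analysis. The stated test cannot give a Deaf-hearing estimate of search ability or knowledge acquisition, although that comparison is the stated goal and the hearing data are to be collected. The literacy grouping is a second, independent inconsistency of wording with consequences for selection and analysis.

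The gain from correction is an estimate with a half-width of about 0.52 SD or 0.75 SD, depending on which stated sample size is right. Neither figure should be treated as settled until the sizes are reconciled. All SD-unit figures rest on a two-sided 5% level and a common SD, which are my assumptions. Even at the larger size the contrast is exploratory, and the interaction would be very imprecise.

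The Deaf-hearing effect would be averaged over the sampled literacy strata. The Background describes Deaf ASL users as nearly 7 times more likely than hearing peers to have inadequate health literacy, so equal strata do not mirror the two populations, and the estimate should not be read as an overall population difference.

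**What to change.** 1. Reconcile the Aim 3 sample size across the Abstract, Study Design, Procedures for Return Visit, Table 2 and Analyses for Aim 3 before specifying any contrast.
2. Make the literacy grouping in Analyses for Aim 3 match the strata actually sampled. If only inadequate (0-1) and adequate (5-6) participants are invited, drop the intermediate level from the test. If people scoring 2-4 are to be invited, say so in the sampling text and use one name for that category throughout.
3. Keep the Deaf-only literacy contrast, which answers the Table 2 question.
4. Add an exploratory linear model for each task measure with hearing status, literacy stratum and their interaction. Report the Deaf-hearing difference, the literacy effect within Deaf participants and the interaction as estimates with 95% confidence intervals. State that the Deaf-hearing effect is averaged over the sampled strata and that the interaction will be very imprecise.

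The cost is a change of wording and a small amount of analysis. Both groups are already due to perform the recorded tasks, so no new measurement is needed; recruitment changes only if reconciling the sample size shows that it must.

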### Analysis of the Elicitation Interviews

For the iterative analysis of the qualitative data obtained with the elicitation interview process, we will follow multiple steps: (1) thoroughly read the transcribed data, (2) generate initial codes, (3) search for themes and patterns among the codes and across participants, (4) review themes, and (5) define and name themes. Initial data queries will focus on questions that emerge from aims 1 and 2 and navigability and knowledge acquisition patterns as measured in step 1. As we learn more through the iterative elicitation interview/analysis process, emerging themes and questions will be explored. Video-recording data of the one-on-one interviews will be transcribed into English by a bilingual transcriber [10]. Field notes will be taken after each encounter to describe the context, primary content, and emerging concepts. Participants’ data in aim 3 will also be linked with the data collected in aims 1 and 2 that helped inform questions in the elicitation interviews. This will be done through the use of joint displays, a state-of-the-art integration procedure in mixed methods studies used for visually matching results by domains and themes from the quantitative and qualitative data to link the relevant information. All raw data video files will be uploaded onto a secure server, transcribed at the PI’s office, and analyzed by the qualitative team. The use of Dedoose software [48] will allow transcription and detailed annotation to be tagged with video data of Deaf signers. All qualitative data (transcripts and field notes) will be coded independently by multiple investigators. Codes will be developed using consensus. A codebook will be created initially using navigation and knowledge acquisition and will be expanded with emergent codes. All transcripts will be coded by the research team (shown above) using the codebook in Dedoose.

## Results

The project received human participants approval from the University of Michigan IRB (HUM00132918) to provide oversight to the 3 other research sites. Data collection will be completed in late 2020. Findings from this study will be used to advance what is known about health literacy and health information accessibility for the Deaf population. The findings will help explain how Deaf individuals access, navigate, and comprehend Web-based information. This study will help guide formulation of health information and health literacy interventions that more accurately take advantage of visual learning skills, even for those who have normal hearing. The findings will also be potentially beneficial for website editors. On the basis of the findings, recommendations for improving accessibility to health information for those who are non-English speaking and for those with inadequate health literacy will be provided. Results will be published in peer-reviewed journals once completed.

## Discussion

### Principal Findings

This project will advance knowledge on the origins of inadequate health literacy among Deaf individuals, including how effectively they access Web-based health information. In this paper, methods developed for the study will help assess the role of information marginalization on health literacy in the Deaf population. We also describe our approach to adapt instruments and measures applicable for Deaf ASL users. This project is the first to systematically explore health literacy for Deaf individuals. Most Deaf studies focus on Deaf health knowledge gaps and disparities, but our goal is to provide tangible recommendations going forward, especially for those involved with health information dissemination and website editors.

### Direct Impact

Improvement in translation work and their processes can have an important impact as it affects other funded research projects and those that are being proposed. Furthermore, existing measures (eg, ASL-NVS) will be shared with other investigators interested in working with this population. We hope that the measures can be incorporated into community and clinical surveillance to help them manage their own health and determine how health information may or may not be reaching these individuals. Research with these communities are highly underfunded. This project provides an example of feasible research with the Deaf community. In addition, little is known about the predictors of health literacy in Deaf populations and how this affects their ability to use Web-based health information. This is key because of their social and information marginalization and their documented risk for inadequate health literacy. Web-based health information, if accessible, can provide a strategic approach to address the community’s health knowledge gaps.

The results of this mixed methods proposal will significantly advance what is known about health literacy and health information accessibility for the Deaf population. This innovative study will generate rich data on how to formulate health information and health literacy interventions more accurately to take advantage of visual learning skills. The study results will be provided once data collection is complete (anticipated in 2020). Once finalized, findings will be used to develop a white paper on how to structure Web-based health information in a way that maximizes accessibility and comprehension for Deaf individuals and also includes strategies that adhere to universal health literacy precautions because of the Deaf population’s documented risk of inadequate health literacy.

